## Abstract

**Background:**

Chile is implementing a Community Mental Health Model with a strong role of primary health care (PHC). PHC has great potential to early detection and provision of accessible and coordinated services to people who present mental illness and/or substance use issues (MISUI). However, stigma toward people with MISUI among PHC professionals is a significant barrier to accessing good quality of care. A wealth of literature supports the importance of reducing stigma for this population. The main goal of this research project is to determine the effectiveness of a comprehensive anti-stigma intervention in reducing stigmatizing attitudes and behaviors among PHC providers toward individuals with MISUI in the Chilean context, using Centros de Salud Familiar (CESFAMs) as the point of intervention.

**Methods:**

The intervention is based on an initiative that was previously developed in Canada and then also pilot-tested in Lima, Peru, with the Center for Addiction and Mental Health (Ontario, Canada). The model will be culturally adapted with CESFAM PHC provider and user inputs to be relevant and valid to Chile. The 18-month intervention includes five (5) components that are simultaneously implemented in CESFAMs: (1) Develop a Team of Local Champions in each intervention CESFAM, comprising PHC providers and users; (2) Analysis of Internal CESFAM Policies, Procedures, and Protocols to determine areas of improvement in service delivery for individuals with MISUI; (3) Raising Awareness of stigma toward MISUI using various forms of media within the CESFAM; (4) Innovative Contact-Based Education workshops on anti-stigma and recovery principles, co-lead by academic/clinical trainers and a person with lived experience of MISUI; and (5) Recovery-Based Arts, a multi-week arts workshop for PHC providers and users to produce artwork related to MISUI and recovery, culminating in an exhibition to showcase artwork for the CESFAM providers, users, and community. The expected intervention outcomes are the following: Participation in the experimental group will result in a significant decrease in stigmatizing attitudes among PHC providers toward individuals with MISUI compared with the control group as measured by the Chilean version of the Opening Minds Scale for Health Care Providers Scale (OMS-HC); Participation in the experimental group will result in a significant decrease of PHC users experiences of stigma conveyed by PHC providers compared with the control group as measured by the Internalized Stigma of Mental Illness (ISMI) scale, validated for the Chilean population. The changes in attitudes and behaviors within the experimental group will be sustained over time as measured at 6 months-follow-up. To evaluate the effectiveness of this 18-month intervention, a 4-year, two-arm, cluster-randomized controlled trial is proposed, with CESFAMs being the unit of randomization (or “cluster”). Implementation Science approach will be taken to measure relevant implementation outcomes for each component of the intervention, and through qualitative data collection with CESFAM providers and authorities. Data analysis will be carried out using SAS 9.4 (specifically, using POC MIXED and PROC GENMOD) and R 3.5. Mixed-effect modeling will used for both PHC provider and user data, which will include individuals and CESFAMs as random effects and group (intervention/control) as fixed effects.

**Discussion:**

This study represents a new stage of relevant and innovative research in mental health and stigma in Chile that will contribute to improving access and quality of care for people with MISUI. Evaluating the impact of the intervention model and its implementation will provide the necessary tools to scale the intervention up to other CESFAMs across Chile.

**Clinical trial registration:**

[www.ClinicalTrials.gov], identifier [NCT05578066].

## Introduction

Chile presents one of the highest mental disorder burdens in the world, with nearly 38.3% of children and adolescents having had mental illness (1); one third of the population having had a psychiatric disorder in their lifetime, and 22.2% in the past year (2). Alcohol dependence accounts for 7.7% of total DALYs in Chile, and unipolar depression and anxiety disorders are at the top five of DALYs among women (3). The high prevalence of mental illness and substance use issues (MISUI) in Chile is confirmed by the results of the 2016–2017 National Health Survey (4). MISUI account for about 19% of global DALYs (5, 6) and in Chile, the longitudinal study “Mental Health Thermometer in Chile: Fifth Round” (2022) (7) concluded that 21.1% of participants suspected to have or had Mental Health Issue and 45.9% declared that they had a worse or much worse mood than before COVID-19 pandemic (7). There has also been an increase in the “sometime in life” consumption of non-prescription tranquilizers, hallucinogens, and pain relievers without a medical prescription in adults (8). The adolescent population is in first place in Latin American ranking of consumption of cocaine, marijuana, cocaine base paste and tranquilizers without a medical prescription (1, 5, 9).

Mental Health has been declared as a component of fundamental health human right, but in Latin America less than 40% of people with Mental Health disorders have received treatment (1). There is a global movement to strengthen and support Primary Health Care (PHC) services, including MISUI treatment (10, 11). The high prevalence of mental disorders among PHC patients and the fact that most patients with MISUI will access the health care system through PHC providers makes it an ideal setting to implement early screening and treatment strategies for these health problems (12). Evidence suggests that PHC may resolve up to 90% of mental health issues (13).

The gap in MISUI treatment represents a long-standing neglect of mental health care, with a variety of factors limiting access to care (14), including (1) PHC services lacking the ability to adequately respond to needs for MISUI treatment, and (2) stigma playing a significant role in the hesitancy of people with MISUI to recognize their condition or seek help (15, 16).

Stigma is a phenomenon comprising negative thoughts and actions toward the bearer, in which “elements of labeling, stereotyping, separating, status loss, and discrimination co-occur in a power situation that allows these processes to unfold” (17). Stigma affects multiple health domains such as social relationships, levels of stress, self-perception opportunities or behavior, and can add to the burden of disease or disability (18, 19).

Factors affecting stigma and discrimination are interacting constantly generating complex experiences of stigmatization (20, 21). In recent years, structural discrimination as well as socio-economic and political factors impacting stigmatized people has been described (21, 22). Professional stigma has also been described, as health professionals emulating socially stigmatized lay perceptions of those with mental illness (23).

Stigma toward people with MISUI is a global public health problem (21, 24, 25), and represents a main challenge in the integration of mental health into PHC (12, 26). People with MISUI are exposed to different stigma manifestations components that interact as an interrelated multilevel system, jeopardizing their mental health (20). MISUI stigma-related attitudes can be defined as the predisposition or tendency to respond that is triggered by a marker of illness (27). MISUI stigma-related behaviors refers to the discriminatory acts that result from the negative attitudes and stereotypes (28). Stigma-related attitudes and behaviors can be experienced in health care settings in various forms, such as being threatened with coercive treatment, being provided with insufficient information, being regarded as lacking the capacity for responsible action and being patronized or humiliated (21, 29).

It is important to recognize that there are differences in the way stigma manifests toward mental illness (MI) and substance use issues (SUI) (30–36). Literature suggests that people with SUI may have worse patient experiences when compared with patients without SUI (26). This represents an important challenge for accessing care for people with MISUI in PHC (37).

Stigmatizing attitudes and actions from health professionals toward those with MISUI are barriers to health care (38, 39) and can lead to individuals with MISUI receiving lower-quality physical health care services than others (40, 41). Figure 1 describes MISUI treatment primary gaps in PHC, which interacts constantly with the sociopolitical and cultural context. There is ample evidence of MISUI stigmatization in health care, such as PHC settings (26, 42), and by health professionals (30–34). Recent (26, 42) studies have found that PHC physicians “don’t take mental illness as seriously as other chronic diseases” and negative attitudes toward people with substance use disorder are common among them (35, 36). These experiences of stigma can have detrimental effects on the quality of life of those receiving care (29, 43) and lead to a reduction of treatment adherence and outcomes, as well as perceived health for MISUI (44, 45). Stigma has also been identified as an important limitation in the help-seeking process (46) and mental health care access (23), also, perceived health care provider stigma may lead to worsened clinical and personal recovery (44, 47).

**FIGURE 1 F1:**
[figure not shown]
Gaps in MISUI treatment in primary health care.

Services for MISUI at the PHC level have potential to minimize stigma and discrimination (23, 46), as people with these conditions are generally treated by the same providers and in the same community-based location as people with other health conditions (48).

There are other health professional-related characteristics limiting the access for optimal mental health care, including (i) poor professional education about MISUI, (ii) lack of training in interpersonal skills, (iii) inadequate time to evaluate and treat mental disorders, (iv) failure to consider psychotherapeutic approaches, among others (39).

The Chilean public health system (Figure 2) serves more than 75% of the population with its highest coverage in the middle- and low-income population groups (49, 50). Health service provision is organized by territory, through 29 Servicios de Salud (health districts) (15, 51). These health districts direct and coordinate activities from prevention to treatment and rehabilitation. They are organized through a hierarchical system that includes Tertiary and Secondary health care levels, as well as PHC (15, 52). Tertiary level has a reduced coverage and high complexity services. Secondary level has a medium coverage and complexity services. PHC provides services with high coverage, having diagnosis and treatment access available for most health problems, including MISUI. There are more than 500 PHC centers, in urban and rural areas, in which doctors, nurses, psychologists, social workers, technicians, and other providers work (53). Chilean PHC centers have implemented a Family and Community Health approach (54), becoming family health centers, or Centros de Salud Familiar (CESFAMs). Health professionals within the CESFAM are organized by territorial areas and provide care for the most common diseases. For MISUI, the CESFAM have the role of making a timely diagnosis, providing a set of treatments (based on clinical practice guidelines), or referring patients to a specialized mental health center (55).

**FIGURE 2 F2:**
[figure not shown]
Chile’s public health care system.

Chile has been at the forefront of integration of mental health and PHC in Latin America (49, 52, 55–57). However, a significant gap for MISUI treatment exists, as only 38.5% of patients in Chile with a psychiatric diagnosis receive any kind of mental health care, whether treatment is provided by a specialist or by PHC (15). According to Chile’s National Mental Health Plan, up to 2017 Chile’s Mental Health budget was close to 2% of the overall Health budget, far below the 5% proposed by World Health Organization (3, 58). Although there has recently been an increase in national interest to enhance Mental Health budget.

The 2017–2025 National Mental Health Plan emphasizes enhancing the community mental health model, with a central role for PHC (3). Chilean PHC has already incorporated effective mental health programs, such as for depression or substance use problems, but there are challenges regarding low adherence levels (51, 53).

It is critical to test context-specific interventions to address stigma in Chilean PHC (2, 59, 60). The 2017–2025 National Mental Health Plan recognizes stigma toward MISUI as an important challenge (3). Evidence based-interventions that can effectively reduce MISUI stigma within health care settings are needed in Chile and worldwide (32, 61). However, a comprehensive, MISUI stigma reduction intervention is required and has not yet been tested or implemented in the Chilean PHC context. This is the first Chilean study to evaluate a comprehensive, multicomponent, anti-MISUI stigma intervention targeting CESFAM providers from an organizational perspective. There was another study specifically aimed at reducing stigma between PHC professional toward people with severe mental disorder diagnosis (62).

One of the projects to address stigma-related attitudes regarding MISUI in the Canadian PHC system was successfully implemented in three Toronto community health centers, resulting in the creation of a comprehensive anti-stigma intervention (21, 63, 64). The intervention proved to be effective at reducing stigmatizing attitudes among health professionals toward people with MISUI. Later on, that intervention was tested in Lima, Peru, after being adapted to the local context (21, 65).

Health care providers are an ideal target group for these interventions, given their clinical interactions with people with MISUI, however, stigma reduction programs for this group are uncommon (66), especially in PHC (61). Interventions comprising training specifically regarding stigma, social contact with users with MISUI, and a focus on recovery are most effective in terms of short-term improvements in stigma (67, 68). There is an important need to follow-up to determine whether positive intervention effects are sustained over time (66, 69). There is a need to actively include those with MISUI in the intervention process and to culturally adapt interventions carried out in settings other than those in which they were designed (70).

A previous related FONDECYT project (34) was just completed, a mixed methods study which sought to examine and understand the phenomenon of stigma toward people with MISUI in the PHC setting of the public health system in Chile. The study confirmed the presence of stigma toward people with MISUI. In addition, it (1) adapted and validated instruments to measure stigma among PHC providers in Chile (71), and (2) identified key elements to be considered for designing an effective intervention to reduce that stigma. In addition, it explored feasibility of the Canadian intervention. This research proposal represents a natural next step aimed at determining the effectiveness of a comprehensive anti-stigma intervention in reducing stigmatizing attitudes and behaviors among PHC providers toward individuals with MISUI in the Chilean context, using CESFAMs as the point of intervention.

## Methods and analysis

### Study design

This two-arm, cluster randomized controlled trial (64) will test the effectiveness of the adapted anti-stigma intervention for MISUI in Chile. As described in Figure 3, CESFAMs will be randomized to control and intervention arms of the study. Situational assessments will be conducted at intervention CESFAM, in order to understand their specific characteristics. A cultural adaptation will also be done at these PHC Centers, through a sequential process based on Barrera y Castro framework (72). Data will be collected in intervention and control CESFAMs on relevant stigma outcomes before (baseline), during (mid-point), and after (end-point) the intervention, as well as 6 months post-intervention (follow-up), to determine the effectiveness of the stigma reduction program. Additionally, data will be collected throughout to evaluate intervention implementation. The intervention stage will last a total of 18 months. This will be consist on five components that will be addressed furthermore. After developing the final integrated analysis, the team will disseminate findings and create a scale up intervention.

**FIGURE 3 F3:**
[figure not shown]
Study design.

This research design is useful for non-clinical interventions that are targeted at health providers and patients, and has been used in PHC settings in the past (73, 74). Because an entire group (or “cluster”) is randomized to either intervention or control, the risk of contamination across trial groups is minimized (75). In the proposed study, the cluster will be the CESFAM, with eight intervention and eight control sites participating in the study. All PHC providers currently employed at the intervention CESFAMs and some PHC users that have received care there for MISUI in the 3 months prior to study participation are the intervention target groups. The intervention will be conducted in selected CESFAMs by the research team and/or dedicated and trained personnel. CONSORT guidelines for cluster randomized trials will be followed in all steps of the study (76).

### Inclusion and exclusion criteria

To be eligible for inclusion in the study, CESFAMs must serve a registered population of at least 15,000 people and have at least 50 staff employed. In addition, the following criteria will be considered: (1) geographic location; (2) characteristics of the population served (e.g., size, ethno-cultural profile); (3) rural or urban areas; (4) willingness to participate.

Exclusion criteria: Being part of another anti-stigma program.

### Sample, recruitment, and randomization of Centros de Salud Familiars

*Servicios de Salud* will be approached and invited to participate. CESFAMs that satisfy the inclusion/exclusion criteria within participating *Servicios de Salud* will be progressively invited to participate in the study. About 50% of CESFAMs in the Metropolitan Region will be recruited, 25% in the North and 25% in the South of Chile. Once the 16 CESFAMs that satisfy the criteria are selected, they will be randomly assigned to intervention and control conditions, within each of the three mentioned geographical areas. The nature of the intervention and cluster randomized design of the study requires application to the entire CESFAM (census approach), not to individual PHC providers.

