#### Specific objective 3: Evaluate the effectiveness of the intervention in primary health care

This part of the interventions is composed by a quantitative and a qualitative component.

1. a Quantitative Component:

All PHC providers at the selected CESFAMs who have direct contact with users will be recruited for the study and will be expected to participate at all data collection time-points. A total sample size of at least 36 PHC providers per CESFAM with a total of 288 per arm its estimate (or 576 per data collection). Sample size for the proposed study was calculated in two steps. First, it was calculated with individual randomization. This calculation was based on the mean ± SD score for the OMS-HC scale was 48 ± 8.3 points, estimated with a sample of 798 PHC providers surveyed in FONDECYT N° 1160099 (34). This should be the average obtained in control CESFAM for the present study. Based on prior interventions in Canada (63), an estimated effect size of 10% in the intervention arm and a placebo effect of 3% in the control arm (from survey application) is expected. Thus, the average OMS-HC score in the intervention arm is expected to decrease to 43.2 ± 8.3 in the intervention group and 46.6 ± 8.3 in the control group (representing a decrease of 4.8 and 1.4 points, respectively). The standard deviation was assumed to remain the same in the intervention and calculations. To detect a statistically significant difference between intervention and control CESFAM, with an α = 5% and statistical power of 80%, the minimum sample size per arm is 94 individuals. Considering a 10% loss to follow-up in the intervention arm, 105 individuals per arm should be recruited with an individual randomization design. The minimum sample size was also calculated considering cluster randomized controlled design. Two elements were considered: (1) a minimum sample size of 105 and (2) an estimation of the intracluster correlation coefficient (ICC) for the study outcome (OMS-HC scale) (83). In this case, it was assumed the ICC to be ρ = 0.05, which is consistent with highest value reported in the literature for outcomes in primary care settings (74) and slightly higher than that reported in a study of a depression program in CESFAMs in Chile (84). Given the required sample size calculated based on individual randomization and the value of ICC = 0.05, the minimum number of clusters required is equal to: [105*0.05] = 5 clusters (75). However, a larger number of clusters would allow recruitment of a smaller number of individuals per cluster, maintaining an α = 5% and statistical power of 80% to detect differences between the control and intervention groups (85). For example, if 8 clusters per arm is considered (16 CESFAM total), it is necessary to recruit a minimum of 36 professionals per CESFAM. Thus, a minimum of the total sample of PHC providers to recruit would be 288 per arm (576 total). The validated, Chilean version of the Opening Minds Scale for Health Care Providers Scale (OMS-HC) (86), will be used as the primary outcome measure for PHC Professionals in the study. It will be applied at baseline, mid-point, end-point, with an expected 9-month interval between applications, and at 6-month follow-up.

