### Data analysis

The data analysis will be conducted through months 42–48. Post data collection activities consider the following: (1) Data cleaning and evaluation, (2) Creation of derived variables, (3) Response rate calculation and (4) Bias evaluation.

It will be carried out using SAS 9.4 (specifically, using POC MIXED and PROC GENMOD) and R 3.5. Mixed-effect modeling will used for both PHC provider and user data, which will include individuals and CESFAMs as random effects and group (intervention/control) as fixed effects. The technique is appropriate to analyze cluster randomized controlled trials because these models can account for the possible dependence between responses of users and PHC providers within the same CESFAM. A descriptive analysis will initially be conducted to obtain a general picture of the sample. Time and important covariates (e.g., demographics) as they relate to our outcome variable will be explored. Univariate association tests will be performed to clarify the unconditional effect of these covariates on outcomes.

After the quantitative and qualitative data have been analyzed, summarized, and interpreted independently, the primary focus of the integrated analysis will be on identifying and discussing to what extend and in what ways the qualitative results help to explain the quantitative results (explanatory design). Implementing a “hybrid” approach (104) that will be used for qualitative data.

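### Randomisation is stratified by area and provider baseline scores are collected, but the stated model names neither; naming both would recover power at almost no cost

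*Protocol article*

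**What the plan says.** Under the heading on sample, recruitment and randomization, the protocol article sets the regional make-up: "About 50% of CESFAMs in the Metropolitan Region will be recruited, 25% in the North and 25% in the South of Chile". It then states that "they will be randomly assigned to intervention and control conditions, within each of the three mentioned geographical areas". The Study design section gives the allocation, "with eight intervention and eight control sites participating in the study". With 16 centres this means strata of about 8, 4 and 4.

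For providers, Specific objective 3 says of the OMS-HC: "It will be applied at baseline, mid-point, end-point, with an expected 9-month interval between applications, and at 6-month follow-up". Users are sampled as separate cross-sections at baseline and end-point, so no user has an individual baseline score.

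The Data analysis section describes one mixed model for both populations, "which will include individuals and CESFAMs as random effects and group (intervention/control) as fixed effects". The Abstract describes the same model. On other terms the section says only: "Time and important covariates (e.g., demographics) as they relate to our outcome variable will be explored", followed by "Univariate association tests will be performed to clarify the unconditional effect of these covariates on outcomes". Area does not appear in the analysis text, and baseline score is not named as a covariate.

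**The concern.** The article states the model's random and fixed effects, and that statement does not match its own randomisation. Stratifying by area removes between-area differences from the treatment contrast. A model without area still counts those differences as error between centres, so the standard error is too large whenever area is related to the outcome.

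Baseline OMS-HC is a separate matter. Randomisation was not balanced on it, so leaving it out does not distort the standard error; it only gives up precision. With 16 clusters and a sample size set at 80% power, that precision is worth having.

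The random effect for individuals raises a third point. It suggests that each provider's repeated scores, baseline included, are outcome rows. If group is then the only fixed effect, its coefficient averages over a visit at which no effect is possible.

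**Working it through.** **Inputs from the protocol (Specific objective 3).** Providers: expected means 43.2 and 46.6 (difference 3.4), SD 8.3, ICC 0.05, 8 clusters per arm, 36 per cluster, 10% loss, 5% alpha (two-sided reproduces the figures), 80% power. Users: 8.79 and 10.23 (difference 1.44), SD 4.74, ICC 0.01, 27 per cluster.

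**Assumed, because the protocol does not give them.** The share s of between-CESFAM variance due to area; the correlation r between baseline and end-point scores, taken as equal at individual and cluster level; equal allocation within each area (4:4, 2:2, 2:2).

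**The plan's own figures.** Providers: n = 2(1.96 + 0.84)² × 8.3² / 3.4² = 94 per arm; 94/0.9 = 105 after loss; cluster size 105 × 0.95 / (8 − 105 × 0.05) = 36.3 (stated 36); 8 × 36 = 288 per arm. Users: the same formula gives 171 per arm (168 with a difference of 1.45; stated 169), and 169 × 0.99 / (8 − 1.69) = 26.5, rounded up to 27. The sample sizes reproduce to within rounding, and nothing in them relies on covariate adjustment.

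**Reference power without area or baseline (providers).** Variance of a cluster mean = 0.05 × 68.89 + 0.95 × 68.89/36 = 3.44 + 1.82 = 5.26. SE of the difference = √(2 × 5.26/8) = 1.147. Noncentral t on 14 df gives power of 78.7%.

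**Area.** With area fitted, the between-CESFAM part becomes (1 − s) × 3.44 and the df fall to 12. The test without area was simulated on 16 cluster means (8/4/4), first with fixed area effects and then with area effects drawn at random. Each pair below is fixed / random.

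| s | Type I error, area omitted | Power, area omitted | Power, area fitted |
|---|---|---|---|
| 0 | 5.0% | 79% | 78% |
| 10% | 4.3% / 4.5% | 79% / 80% | 80% |
| 30% | 2.8% / 3.7% | 80% / 83% | 86% |
| 50% | 1.7% / 2.9% | 81% / 85% | 91% |

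With area fitted, type I error stays at about 5% throughout. Users, by noncentral t: 74.4% without area when s = 0; with area fitted, 73.3%, 76.1% and 78.0% at s = 0, 30% and 50%.

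**Provider baseline.** Multiplying the variance by (1 − r²), with s = 0 and 14 df, gives SE 1.094, 0.993 and 0.819 for r = 0.3, 0.5 and 0.7. Power is 82.3%, 88.9% and 97.1%, a gain of about 4, 10 and 18 points over 78.7%. The comparator is an end-point-only test. Spending one more df (13) on a CESFAM baseline mean lowers each figure by less than 1 point.

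**Dilution.** With complete data at four visits, no effect at baseline and 3.4 points at each later visit, a group-only coefficient estimates (0 + 3.4 + 3.4 + 3.4)/4 = 2.55.

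**The case against.** The strongest reply is that this is silence, not exclusion. The Data analysis section is a short summary in a journal article, its list of effects need not be complete (time is missing from it although providers are measured four times), and covariates are to be explored. A separate analysis plan may name area and baseline. That stands to this extent: the document does not say that area or baseline will be left out, so the accurate statement is that it names neither. It does not remove the point, because exploration commits to no adjustment set and the model as stated does not reflect the randomisation.

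The second reply is that nothing is lost relative to the plan. The sample size reproduces without adjustment, and power with area omitted does not fall as the area share rises. This is correct. The loss is of power that the design makes available, and its size rests on assumed values.

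Three stronger readings are tempting, and the document does not support them:

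- A reader might infer that leaving out baseline also makes the test conservative. It does not; that applies to area only, and only if area is prognostic.
- A reader might infer that the univariate association tests will select covariates for the primary model. The text gives their purpose as describing unconditional effects and says nothing about selection.
- A reader might expect baseline adjustment to lift provider power from the mid-70s to 95% or more. That needs high assumed correlations and an end-point-only comparator that the Data analysis section does not describe.

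**Conclusion.** The point holds as a recommendation on efficiency and specification. It does not show a false-positive risk. The randomisation is stratified by area, the stated model names only group as a fixed effect, and neither area nor provider baseline is named.

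The size is conditional. For area shares of 10-50%, type I error is about 4.5% at the low end and between 1.7% and 3% at the high end, and the power forgone is about 0-10 points. At a share of zero the test keeps its 5% level and fitting area costs about 1 point. The potential gain therefore clearly exceeds the potential cost. Provider baseline is worth about 4-18 points for r = 0.3-0.7, as precision only. The dilution from 3.4 to 2.55 arises only if baseline scores are outcome rows and no time or group-by-time term is fitted, which the stated model allows but does not settle.

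**What to change.** In the Data analysis section:

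- Name area (three levels) as a fixed effect in both primary models.
- For providers, specify either a constrained-baseline model with time and group-by-time terms, or the end-point OMS-HC score adjusted for baseline OMS-HC.
- For users, adjustment for the CESFAM baseline ISMI mean is optional; the expected gain is about 1 point.
- If a separate analysis plan already specifies these terms, align the article's description with it.

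The cost is analysis wording, two cluster-level degrees of freedom for area (14 to 12), and one more for any CESFAM-level baseline mean. No further data or centres are needed.
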